### 2.7. Outcome Measures

#### 2.7.1. Primary Outcome

**Hand-washing behavior.** The primary outcome is the percentage of households washing hands. The outcome measure will be obtained by means of a self-developed WASH questionnaire, which involves both multiple choice questions and spot checks (Table S4). 

Spot checks will be used to determine the hardware situation in the household. Assessors will check whether there is a hand-washing station available, and if so, what type of hand-washing station (i.e., running water or a bucket). Spot checks will also be used to determine the presence of water and/or soap at the time of the measurement. By means of the questionnaire, assessors will probe when people normally wash their hands (i.e., before eating, after using the latrine, etc.), and what they use for hand-washing (i.e., water and/or soap). 

A household was defined to have correct hand-washing behavior when they: (1) have a hand-washing station available (spot check), (2) have water and soap available at the hand-washing station (spot check), and (3) indicate that they wash their hands with water and soap (questionnaire). All items must be present. The analysis will be repeated for each of the critical times. Critical times of interest include: after defecation or using the latrine, before cooking or handling food, before eating, and before feeding a child.

#### 2.7.2. Secondary Outcomes

**Latrine use.** Latrine use is assessed by means of a self-developed WASH questionnaire, involving both multiple choice questions and spot checks (Table S5).

Spot checks will be used to check whether there is a latrine available at the household, and if so, what the latrine looks like (i.e., does it have a roof, a door, etc.), and to determine the latrine cleanliness. By means of the questionnaire, behavioral information about the past two weeks is gathered. These questions probe whether people (1) normally use a latrine when defecating at home; (2) normally use a latrine when defecating elsewhere (i.e., when at work in the field); (3) sometimes defecate in the open when at home; (4) sometimes defecate in the open when they are elsewhere; (5) clean the latrine and how often.

A household is defined to have correct latrine use behavior when: (1) they have a latrine available (spot check), (2) the latrine minimally includes walls, a roof, a door or curtain, and a slab or concrete floor (spot check), (3) the latrine is clean (spot check), (4) they indicate to normally use the latrine when defecating at home (questionnaire), and (5) they indicate to not defecate in the open when they are at home (questionnaire). A similar analysis will be performed for latrine use behavior when people are elsewhere.

**Health.** Health is assessed using a self-developed health questionnaire (Table S6). The questionnaire is used to probe the prevalence rates of diarrhea, vomiting, limitations of daily activities, the need for medical care due to diarrheal illness in the past two weeks, and hospitalization due to diarrheal illness in the past three months. The WHO definition will be used: ‘Diarrhea is defined as the passage of three or more loose or liquid stools per day or more frequent passage than is normal for the individual. Frequent passing of formed stools is not diarrhea, nor is the passing of loose, pasty stools by breastfed babies’. Prevalence is subdivided in people below and above 5 years of age.

**Infrastructure.** WASH infrastructure is assessed using a self-developed questionnaire and spot checks (Tables S4 and S5). Both hand-washing and latrine infrastructure will be judged.

The quality of the hand-washing infrastructure is scored based on the type of hand-washing facility (i.e., running water versus bucket) (spot check), the presence of water and/or soap (spot check), and whether or not the station is always operational (questionnaire).

The quality of the latrine infrastructure is scored based on the type of facility (i.e., does it have a roof, a door, etc.) (spot check), the cleanliness (spot check), and the number of people who use the latrine (questionnaire). Information about whether or not the pit has ever been emptied, and how will also be gathered (questionnaire) as this will allow for the measurement of Sustainable Development Goal (SDG) 6 according to the WHO/UNICEF JMP (https://washdata.org) tools.

**Quality of Life.** The EQ-5D-3L is a validated questionnaire, examining 5 dimensions: Mobility, self-care, usual activities, pain/discomfort, and anxiety/depression (Figure S1). All items are scored on a 3-point Likert scale. Results of the EQ-5D-3L can be used to calculate the quality-adjusted life-year (QALY), a generic measure of disease burden. The cost per QALY will be used to determine the cost-effectiveness of each intervention arm.

**Demographics.** Demographic data will be gathered, including the Global Positioning System (GPS) location of the household, village and sub-village, name, age, gender, and education level of the household head. These demographics are crucial to verify that the correct households—i.e., the households that were randomly selected in R—are targeted at each of the intervention and data collection moments. In addition, socio-economic data is collected, i.e., age and gender of the respondent, main source of income, etc. The questionnaire is available in Table S7.

**Compliance.** Compliance to the intervention will be monitored in real-time using KoboToolbox (https://www.kobotoolbox.org/). Monitoring will involve (1) number of household visits provided, (2) number of community sessions provided, (3) number of people who have been reached, (4) duration, (5) content of the sessions/visits, and (6) compliance of the participants. 

### 2.8. Data Analysis

Statistical analyses will be undertaken using R studio (Version 1.0.143). All analyses will be conducted on an intention-to-treat principle using all randomized participants. Demographic characteristics and baseline data will be summarized by descriptive statistics using means, standard deviations and 95% confidence intervals for continuous variables, median and inter-quartile ranges for non-normal continuous or ordinal data and percentages for categorical data. The primary and secondary outcome measures will be analyzed using generalized linear mixed models with baseline values as a covariate to assess differences between treatment groups and across time. A sensitivity analysis will be performed comparing effectiveness of the interventions in low compliance versus high compliance households. All data will be adjusted for multiple comparisons. A *p*-value < 0.05 will be considered as statistically significant.

Investigators who are involved in data analysis will be blinded to group allocation. In accordance to the European General Data Protection Regulation (GDPR) law, all private information (i.e., name or GPS) will not appear on any documents except a participant key. This key is needed to match baseline data with midline, end-line, and follow-up data. A pseudonym will be used to protect participants’ identities. The key linking the participant name to the data is not accessible to the investigators and will be destroyed after data analysis is complete.

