##### Contextualized Intervention Cohort

The contextualized intervention cohort will receive nine household visits of 20–40 min each, at a frequency of one visit every two months. The content of these add-on visits is based on the ‘Risks, Attitudes, Norms, Abilities, Self-regulation’ (RANAS) model (www.ranasmosler.com) [16]. The RANAS model consists of five behavioral factors, which are considered to be the drivers of WASH behavior [16] (see Figure 2). In a preparatory phase, RANAS dictates that questionnaires and interviews are used to better understand the context at play, i.e., do people in the intervention area wash their hands and why (not)? In a second phase, this data is used to develop the intervention, thus optimally tailoring the program to the needs in the community [16,34].

Concretely, baseline data are first gathered through a questionnaire (Table S2). Then, these data will be analyzed to compare (1) people who always wash hands after defecation (do’ers) to people who don’t (non-do’ers); and (2) people who always use the latrine (do’ers) to people who do not (non-do’ers). Do’ers were defined as people who always wash their hands or use the latrine. Non-do’ers were defined as people who wash their hands or use the latrine most of the time, sometimes, seldom or never. Only those behavioral factors (i.e., ‘Risks, Attitudes, Norms, Abilities, and/or Self-Regulation’), that are significantly different between “do’ers” and “non-do’ers” will be included in the intervention, as these are, at least theoretically, considered to be decisive for hand-washing and latrine use behavior in the current setting [16,34]. This implies that the precise content of the intervention can only be determined after baseline data collection has taken place.

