##### Non-Contextualized Intervention

The non-contextualized intervention cohort will also receive nine household visits of 20–40 min each, at a frequency of one visit every two months. The content of these visits involves a general WASH intervention which is not tailored to the context at hand. Based on a study by Mosler et al., who suggested that norms are a universal driver (i.e., not context specific) of hand-washing behavior [35] and other studies and expert input stating that norms of local leaders, in particular, are important in African culture in inducing behavioral change [36,37,38], the focus would be non-contextualized intervention on norms. Concretely, the ‘Norm Behavior Change Techniques’ from the RANAS manual (www.ranasmosler.com) were used to outline the intervention [16]. These interventions encourage participants to improve their hand-washing and sanitation infrastructure and behavior in order to become a WASH role model within their community. A detailed outline of the non-contextualized intervention can be found in Table S3.

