##### Control

The control cohort will receive one household visit of 20–40 min. During this visit, a placebo poster will be distributed focusing on malaria nets. The main goal of this household visit is to avoid jealousy among the control cohort.

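### The planned low- versus high-compliance comparison is observational: it can show a difference in effectiveness with no true effect, and should be reported as descriptive only

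*Protocol article*

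**What the plan says.** Section 2.8 of the protocol article first sets a general rule: "All analyses will be conducted on an intention-to-treat principle using all randomized participants". It then specifies mixed models with the baseline value as a covariate for the primary and secondary outcomes, and adds: "A sensitivity analysis will be performed comparing effectiveness of the interventions in low compliance versus high compliance households".

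The Compliance paragraph of Section 2.7.2 says how compliance is obtained: "Compliance to the intervention will be monitored in real-time using KoboToolbox". Six items are logged. They include "number of household visits provided", the number of community sessions, the number of people reached and the duration. The last item is the compliance of the participants.

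The arms differ in what there is to comply with (Section 2.5.2):
- Contextualized arm: "The contextualized intervention cohort will receive nine household visits of 20–40 min each, at a frequency of one visit every two months".
- Non-contextualized arm: "The non-contextualized intervention cohort will also receive nine household visits of 20–40 min each".
- Control arm: one visit, at which "a placebo poster will be distributed focusing on malaria nets".

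Section 2.5.1 gives the basic package to all three cohorts.

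**The concern.** Randomization balances households between arms. It does not balance households that turn out to be well or poorly reached within an arm. Households that are at home, motivated or better off may keep more visits. They may also be more likely to have a station stocked with water and soap, which is what the spot checks for the primary outcome record. A low/high split can then show a gradient that comes from who the households are, not from what the visits did.

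The label adds to the problem. A sensitivity analysis asks whether the intention-to-treat result survives other reasonable assumptions about the same question. This split asks a different question, the effect among those who complied. It also sits poorly with the rule, in the same paragraph of the plan, that every analysis is by intention to treat.

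At stake is a secondary conclusion: whether the report may say that the add-on visits work when they are delivered or accepted.

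**Working it through.** **The plan's own figures.** Section 2.3 uses 5% versus 20%, two-sided alpha 0.025 and 80% power. The pooled-variance formula without continuity correction gives

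n = [2.241 × √(2 × 0.125 × 0.875) + 0.842 × √(0.05 × 0.95 + 0.20 × 0.80)]² / 0.15² ≈ 91.1, so 92 per group.

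The inflation factor is 400/92 = 4.35, and the ICC is (4.35 − 1)/44 = 0.076. All three reproduce. The present point does not depend on them. The article gives no figure for compliance.

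**Step 1: what the contrast estimates.** Let H and L be the hand-washing prevalence in high- and low-compliance households of an active arm, and C the prevalence in the control arm. With one common control arm,

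(H − C) − (L − C) = H − L.

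The control arm cancels. H − L compares households within one arm, grouped by something recorded after allocation, so randomization does not protect it.

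**Step 2: size under a true effect of zero.** Inputs:
- p, prevalence in both arms: 5% or 20%, the two rates in Section 2.3. Using 20% for control is an assumption; control also receives the basic package.
- f, share of high-compliance households: 0.5 or 0.7 (assumed).
- R = H/L: 1.5, 2 or 3 (assumed).

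No effect means fH + (1 − f)L = p, so L = p/(fR + 1 − f) and H = R × L.

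| p | R | f | L | H | H − C (points) | L − C (points) | H − L (points) |
|---|---|---|---|---|---|---|---|
| 5% | 1.5 | 0.5 | 4.0% | 6.0% | +1.0 | −1.0 | 2.0 |
| 5% | 1.5 | 0.7 | 3.7% | 5.6% | +0.6 | −1.3 | 1.9 |
| 5% | 2 | 0.5 | 3.3% | 6.7% | +1.7 | −1.7 | 3.3 |
| 5% | 2 | 0.7 | 2.9% | 5.9% | +0.9 | −2.1 | 2.9 |
| 5% | 3 | 0.5 | 2.5% | 7.5% | +2.5 | −2.5 | 5.0 |
| 5% | 3 | 0.7 | 2.1% | 6.3% | +1.3 | −2.9 | 4.2 |
| 20% | 1.5 | 0.5 | 16.0% | 24.0% | +4.0 | −4.0 | 8.0 |
| 20% | 1.5 | 0.7 | 14.8% | 22.2% | +2.2 | −5.2 | 7.4 |
| 20% | 2 | 0.5 | 13.3% | 26.7% | +6.7 | −6.7 | 13.3 |
| 20% | 2 | 0.7 | 11.8% | 23.5% | +3.5 | −8.2 | 11.8 |
| 20% | 3 | 0.5 | 10.0% | 30.0% | +10.0 | −10.0 | 20.0 |
| 20% | 3 | 0.7 | 8.3% | 25.0% | +5.0 | −11.7 | 16.7 |

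In general H − C = p(R − 1)(1 − f)/(fR + 1 − f), which is zero at R = 1.

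**Step 3: are such ratios plausible?** A simulation gave compliance and hand-washing a shared latent factor and no intervention effect, and split compliance at its median. A latent correlation of 0.2 gave 6.6% versus 3.3% at 5% prevalence, and 24.5% versus 15.4% at 20%. These ratios, about 2.0 and 1.6, lie inside the assumed range. At 0.4 and 5% prevalence the ratio went beyond it (8.2% versus 1.8%). At zero correlation there was no gap.

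**Step 4: how often would it mislead?** With 400 analysed households in the arm, a simple high-versus-low test at 0.05, ignoring clustering, is significant in about 10% to 63% of trials at 5% prevalence and 39% to over 99% at 20%. A high-versus-control test at 0.025, with the design effect of 4.34, is significant in only about 2% to 6% and 3% to 19%. The risk lies mainly in the high-versus-low contrast, which is the one the plan names.

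**Step 5: a randomized alternative under the same null.** A complier-average estimate is the intention-to-treat difference divided by the difference between arms in the share reaching a visit threshold. Control is offered no add-on WASH visits, so its share is zero. With no effect this is 0/f = 0, however strongly compliance follows hand-washing propensity.

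**The case against.** The strongest reply is that the split is supportive and that one sentence in an article does not fix its cut-off, estimator or control counterpart. Those details can properly sit in an analysis plan that is not shown. This stands as far as details go, and their absence is not criticised here. No choice of cut-off, however, turns a split on add-on compliance into a randomized comparison.

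Several stronger readings are tempting, and the document does not support them.

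- A reader might infer that control households cannot show compliance at all. They receive the basic package and one visit, and compliance with those can be recorded. Only compliance with the nine add-on visits has no counterpart.
- A reader might infer that compliance is the household's choice. Most of the six logged items describe delivery by volunteers; only the last is plainly participant behaviour. The concern still applies if delivery is related to hand-washing propensity, but the motivation argument is then weaker.
- A reader might infer that a dose-response pattern is bound to appear. The bias is zero if compliance and delivery are unrelated to hand-washing.
- A reader might set a high-minus-low gap against the planned 15-point effect. That is not like for like; the arm-versus-control counterpart is the high-minus-control difference.

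The planned baseline covariate also helps, and the illustration ignores it. It removes the bias only in part: at the assumed 5% baseline prevalence, about 95% of households share the same baseline value, so it separates them poorly.

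Finally, an instrumental-variable estimate has weaknesses of its own. Whole sub-villages are allocated together, and the non-contextualized visits aim to make participants role models for their community. Some benefit to poorly visited households is therefore intended. This is a fair reason not to make such an estimate a compulsory replacement.

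**Conclusion.** The point holds in a limited form. If active households are split by add-on compliance, the planned contrast is observational and can show a difference in effectiveness when there is none. The condition is that compliance or delivery is related to hand-washing propensity after baseline adjustment.

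The document does not give the size. Before baseline adjustment, under the assumed ratios and shares, the spurious high-minus-control difference is about +0.6 to +2.5 points at 5% prevalence and +2.2 to +10 points at 20%. Set against the planned 15-point effect, the upper ends are 2.5/15 = 17% and 10/15 = 67%. They are illustrations, not predictions.

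A reader might infer that the trial's main result is compromised. It is not: the primary analysis uses all randomized households by intention to treat and does not use the split. What changes is what the trial may conclude about the add-on in households that complied.

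**What to change.** 1. In Section 2.8, stop calling the split a sensitivity analysis of effectiveness. Report low- and high-compliance households as supplementary, descriptive and non-causal, and draw no conclusion from the split that the add-on works when delivered.
2. If an effect under compliance is wanted, add a supplementary complier-average estimate for each active arm against control. Use the randomized arm as instrument and a binary, pre-stated threshold of add-on WASH visits received as exposure. Adjust for baseline and the randomization strata, cluster standard errors by sub-village, and apply a small-sample correction because there are only nine sub-villages per arm.
3. State the exclusion restriction next to that estimate, and say that visits below the threshold and spillover within sub-villages may both violate it.

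The first step costs a change of wording. The second costs one model per active arm on data already being logged. Its downsides are reliance on the exclusion restriction and a wider interval: dividing by a share of 0.7 or 0.5 widens the interval around the intention-to-treat difference by about 1/0.7 = 1.4 or 1/0.5 = 2 times.

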### 2.3. Sample Size Calculation

The primary outcome of the study is the prevalence of hand-washing after defecation or latrine using. This prevalence will be compared between intervention and control groups at post-intervention. Since we have an interest in comparing both interventions groups separately, the alpha-level will be set at 0.025 (0.05/2).

The sample size estimate was based on the literature and earlier pilot work, which assumed that 5% of the households wash their hands after defecation, at a baseline, and a 15% improvement is expected following contextualized and non-contextualized interventions. To detect an increase in hand-washing prevalence after defecation or latrine using 5% to 20%, 92 households are needed per group to have 80% power, based on a two-sided Chi-square test (α = 0.025). However, the drop-out rate and intra-cluster correlation (ICC) still need to be taken into account. The ICC refers here to the potential correlation in the probability of hand-washing between the households of the same sub-village. The inflation in sample size due to the ICC is given by 1 + ICC*(*m −* 1), where *m* equals the mean number of households per sub-village. 

With 500 households per group (clustered in 9 sub-villages), including a drop-out rate of 20%, the variance inflation factor should be maximal 4.35 (400/92), corresponding to an ICC of 0.076 (4.35 = 1 + 0.076 × (45 − 1)). This closely corresponds to the most conservative estimate found in literature for a comparable outcome [27,28,29]. The calculation is also conservative, since the analysis will be based on a longitudinal statistical model, including data from earlier time points for drop-out participants and the baseline measurement will be used as a covariate. These further increases the power of the study. In conclusion, a total sample of 1500 households were included, i.e., 500 households per cohort. A detailed overview can be found in Table 1.

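### The primary test family that section 2.3 defines and powers is not carried into sections 2.7.1 and 2.8, so the stated 80% power holds only under the narrowest reading of the analysis

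*Protocol article*

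**What the plan says.** Three sections of the protocol article bear on what the primary test is.

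- **Section 2.3 (Sample Size Calculation)** names one critical time: "The primary outcome of the study is the prevalence of hand-washing after defecation or latrine using". Intervention and control groups are to be compared once, post-intervention. Because each intervention is of separate interest, "the alpha-level will be set at 0.025 (0.05/2", with the bracket showing the split over two comparisons.
- **Section 2.7.1 (Primary Outcome)** is broader: "The primary outcome is the percentage of households washing hands". It defines correct hand-washing by two spot-check items and one questionnaire item, then adds "The analysis will be repeated for each of the critical times". Four critical times are listed and none is marked as primary. The primary objective at the end of the Introduction also refers to critical times in the plural.
- **Section 2.8 (Data Analysis)** plans generalized linear mixed models with the baseline value as covariate "to assess differences between treatment groups and across time". It names no visit for the primary contrast. It then states "All data will be adjusted for multiple comparisons", followed by a threshold of p < 0.05.

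Section 2.6 gives three post-baseline rounds: May 2019 and May 2020, after one and two years of intervention, and May 2021, one year after the intervention stops.

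**The concern.** A reader of section 2.3 finds a primary family of two tests. A reader of sections 2.7.1 and 2.8 finds four critical times, three rounds and an adjustment that, taken at its word, spans everything. These are different analyses, and only the first was powered.

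Two things are at stake. First, a broad adjustment makes the per-test threshold much stricter than 0.025, and the planned power no longer applies. Second, with no critical time singled out in the outcome section and no visit in the analysis section, the headline result could be chosen after the data are seen. Even the section 2.3 visit is not fully pinned down, since the May 2020 and May 2021 rounds both come after the intervention period and either could be called post-intervention.

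**Working it through.** **Inputs, all from section 2.3:** rates 5% and 20%; two-sided chi-square test; alpha 0.025; power 80%; 500 households per group; 20% drop-out; 9 sub-villages per group; 45 households per sub-village in the inflation formula; ICC 0.076. Four critical times come from section 2.7.1 and three post-baseline rounds from section 2.6.

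**Step 1. Reproduce the plan's figure.** With pooled variance and no continuity correction:

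n = [z(1−α/2)·√(2·p̄·q̄) + z(0.80)·√(p₁q₁ + p₂q₂)]² / (p₂ − p₁)²

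- p̄ = (0.05 + 0.20)/2 = 0.125, so √(2 × 0.125 × 0.875) = 0.4677
- √(0.05 × 0.95 + 0.20 × 0.80) = √0.2075 = 0.4555
- z(0.9875) = 2.2414 and z(0.80) = 0.8416
- n = (2.2414 × 0.4677 + 0.8416 × 0.4555)² / 0.15² = 1.4317² / 0.0225 = 91.1, rounded up to **92**

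Inflation: 500 × 0.8 = 400; 400/92 = 4.35; (4.35 − 1)/44 = 0.076. In the other direction, 92 × (1 + 0.076 × 44)/0.8 = 92 × 4.344/0.8 = 499.6, that is 500. Every figure in section 2.3 agrees.

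**Step 2. Which family do those figures belong to?** Alpha 0.025 is 0.05/2, so the 80% belongs to two tests: two comparisons with control, one critical time, one visit.

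**Step 3. Keep the sample and widen the family.** With 92 effective households per group and Bonferroni over k tests (α = 0.05/k):

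power = Φ{[0.15·√92 − z(1−α/2)·0.4677] / 0.4555}, where 0.15·√92 = 1.4388

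| Family | k | α per test | z | Power | n for 80% | Per group after inflation (n × 4.344/0.8) |
|---|---|---|---|---|---|---|
| 2 comparisons, 1 critical time, 1 round (section 2.3) | 2 | 0.025 | 2.241 | 80% | 92 | 500 |
| 2 comparisons × 3 rounds | 6 | 0.00833 | 2.638 | 67% | 117 | 636 |
| 2 comparisons × 4 critical times | 8 | 0.00625 | 2.734 | 64% | 123 | 668 |
| 2 × 4 × 3 | 24 | 0.00208 | 3.078 | 50% | 148 | 804 |

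Worked for k = 8: (1.4388 − 2.734 × 0.4677)/0.4555 = 0.351, and Φ(0.351) = 0.64.

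**Assumptions in step 3.** The documents give 5% versus 20% only for hand-washing after defecation or latrine use; using it for the other critical times is an assumption. Bonferroni ignores correlation between the tests. The documents do not state that 6, 8 or 24 tests form one family; the table shows what follows if the adjustment is read that broadly.

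**The case against.** Three stronger readings are tempting, and the documents support none of them.

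- *That 0.025 and 0.05 contradict each other, so the type I error is inflated.* In section 2.8 the adjustment sentence comes immediately before the 0.05 threshold. P-values adjusted for two comparisons by Bonferroni and judged at 0.05 are the same rule as 0.025 per comparison. An unadjusted 0.05 is not what the text describes. What is unclear is the family over which the adjustment runs.
- *That the 80% power belongs to no defined test.* Section 2.3 defines the test well enough to reproduce 92 exactly. The fault is that later sections do not repeat it.
- *That section 2.8 plans an effect pooled over rounds.* Section 2.3 itself foresees a longitudinal model with baseline as covariate, and a single-visit contrast can be estimated from such a model. Nothing in the article proposes a pooled effect.

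The defence goes further. Repeating an analysis fits a base analysis already named in section 2.3. The adjustment could mean only the contrasts between arms within each outcome. The four critical-time outcomes share the same two spot-check items, so they must be related and Bonferroni overstates the loss. Section 2.3 also calls its calculation conservative, because of the baseline covariate and the use of earlier data from drop-outs, though it does not quantify the gain. Finally, an article may leave the adjustment method to an analysis plan.

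Most of this stands, and it makes the lower power figures illustrative. It does not remove the mismatch. The method can be left to another document, but the article states the primary outcome in two ways and fixes an adjustment rule that, as worded, reaches well beyond the two powered tests.

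**Conclusion.** The point holds as an inconsistency between sections. Section 2.3 defines and powers two tests, section 2.7.1 widens the primary analysis to four critical times, and section 2.8 names no primary visit and adjusts without limit.

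The 80% (80.4% at 92 effective households per group) is valid for the two-test family only. Power is about 64% if the adjustment extends to the four critical times, and about 50% if it also extends to the three rounds. Both are lower figures that rest on Bonferroni, equal rates for every test and no allowance for correlation; the true loss under a broad adjustment would probably be smaller. The freedom to choose the critical time and round afterwards does not depend on those assumptions.

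This is more than missing detail, because the choice of family decides whether the stated power applies and which result counts as the trial's answer.

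**What to change.** Carry the section 2.3 test into sections 2.7.1 and 2.8:

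- Name as the sole primary family hand-washing after defecation or latrine use at the end-of-intervention round (May 2020), each intervention versus control, estimated from the longitudinal model. State the same round in section 2.3.
- Test each comparison at 0.025 or, equivalently, adjust p-values for two comparisons and judge them at 0.05.
- Make the other three critical times and the May 2019 and May 2021 rounds secondary, outside the primary adjustment.
- Replace the sentence "All data will be adjusted for multiple comparisons" with this rule.

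The cost is wording, settled before the May 2020 data are analysed. No sample size or data collection changes. The downside is that the other critical times and rounds become secondary. The direct comparison of the two interventions, which was not part of the family powered in section 2.3, also stays outside the primary family.
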